### Study design and randomization

This study is a RCT. Participants will be randomly divided into the intervention or control group. In order to preclude that the effects arise only from the intensified social contacts during intervention, the control group within a residency will come together three times a week for tea or other sedentary activities, e.g. watching television. The Medical Ethical Committee of VU university medical center approved the study. Oral and written informed consent will be obtained from all participants or their relevant relatives prior to their enrolment.

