### Recruitment

Participants for this study will be recruited via medical staff of aged care facilities. First, the medical staff will be informed about the goal and procedure of the study. Secondly, possible participants will be selected within subunits of the institutions by a team, including the researcher, medical staff and nurses. Third, an information letter with informed consent will be sent to the legal representatives of the participants, together with an invitation to attend an oral presentation. Fourth, once written consent is received, subunits make a schedule for assistants to accompany the regular walks of participants in the intervention group.

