### Procedure

The outcome variables are measured at baseline (pre-treatment: T0), after 6 weeks of intervention (post-treatment: T1) and after 3 (T2), 6 (T3), 9 (T4), 12 (T5) and 18 (T6) months of intervention. Trained experimenters, blinded to the intervention assignment, will administer the neuropsychological tests, physical tests and level of depression, anxiety and pain. The nursing staff fills in questionnaires to measure QoL, ADL and define the stage of dementia. The other variables are objective measurements.

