### Statistical analysis

Comparability between the intervention group and the control group will be assessed at baseline to check for differences between the groups on characteristics that may influence the results on the outcome variables. Scores on neuropsychological tests will be converted into z scores and, according to factor analysis, summed up to form specific cognitive domains. A two-way repeated measurement design (T1-T6), with time as within group factor and group (intervention vs control) as between group variable, will be used to analyse the effect of the intervention on the outcome variables.

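### The stated time-by-group model leaves out residence or subunit, although recruitment and the control sessions are organised by them, so its standard errors do not reflect that structure.

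*Protocol article*

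**What the plan says.** - **Model.** The Statistical analysis section describes "A two-way repeated measurement design (T1-T6", "with time as within group factor and group (intervention vs control) as between group variable". No residence, subunit or institution term is named.
- **Allocation.** Study design and randomization says: "Participants will be randomly divided into the intervention or control group". It mentions no blocking or stratification by residence.
- **Control condition.** The same section says that "the control group within a residency will come together three times a week for tea or other sedentary activities". This is delivery in groups, by residence. It also implies that a residence with controls may hold walkers too.
- **Recruitment and walks.** Under Recruitment, "possible participants will be selected within subunits of the institutions by a team", and "subunits make a schedule for assistants to accompany the regular walks of participants in the intervention group".
- **Raters.** Under Procedure: "The nursing staff fills in questionnaires to measure QoL, ADL and define the stage of dementia".
- **Planning.** Sample size gives 70 per group from f = 0.32, alpha 0.05, power 0.80, seven measurements and two groups, with no allowance for clustering.

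**The concern.** A model with only time and group treats participants as independent apart from the repeated measures on each person. Settings here range from day care to nursing homes, so participants from the same place are likely to resemble each other. Two consequences follow, in opposite directions.

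If both arms are present in each residence, differences between residences largely cancel from the comparison of arms. The model still counts them as error, so the test is somewhat conservative and precision is given away. If meeting as a group makes controls in the same residency more alike, the control mean is less precise than the model assumes and the test is somewhat liberal. A reader of the results could not tell which effect dominates, although the variable needed to deal with the first is known from recruitment.

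**Working it through.** **1. The plan's own figure.** A multivariate repeated-measures test of the time-by-group interaction with seven measurements has df1 = 6. At N = 140, df2 = 140 - 2 - 6 + 1 = 133 and the noncentrality is f² × N = 0.1024 × 140 = 14.34. Power is 0.802 and N = 140 is the smallest total reaching 0.80, so the 70 per group is reproduced. That calculation assumes independent participants, as the stated model does.

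**2. Inputs that must be assumed.** Residence ICC 0.05 to 0.15, control-session ICC 0.05 to 0.10 and control groups of 6 are illustrative. The ICCs refer to the quantity tested, a participant's mean over T1-T6, and the arms are taken as equal in size.

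**3. Residence omitted, both arms equally represented in each residence.** The true variance of the group difference is (1 - ICC) times what the model reports.

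| Residence ICC | Reported SE / true SE = 1/√(1 - ICC) | True alpha = 2[1 - Φ(1.96/√(1 - ICC))] |
|---|---|---|
| 0.05 | 1.026 | 0.044 |
| 0.15 | 1.085 | 0.034 |

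For a comparison with 0.80 power when residence effects are ignored, power without the term is Φ(0.842/√(1 - ICC)) = 0.81 to 0.82. With the term it is Φ(2.80/√(1 - ICC) - 1.96) = 0.82 to 0.86.

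**4. Control sessions only, no residence effect.** The control arm has design effect 1 + (6 - 1) × ICC and the walking arm has 1. The variance ratio for the difference is their average.

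| Session ICC | Control design effect | Variance ratio | True alpha = 2[1 - Φ(1.96/√ratio)] |
|---|---|---|---|
| 0.05 | 1.25 | (1 + 1.25)/2 = 1.125 | 0.065 |
| 0.10 | 1.50 | (1 + 1.50)/2 = 1.25 | 0.080 |

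**5. Both together,** with 6 walkers and 6 controls per residence. Walkers contribute 1 - ICC(residence). Controls contribute 1 - ICC(residence) - ICC(session) + 6 × ICC(session).

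| Residence ICC | Session ICC | Variance ratio | True alpha |
|---|---|---|---|
| 0.15 | 0.05 | (0.85 + 1.10)/2 = 0.975 | about 0.047 |
| 0.10 | 0.05 | (0.90 + 1.15)/2 = 1.025 | about 0.053 |
| 0.05 | 0.10 | (0.95 + 1.45)/2 = 1.20 | about 0.074 |

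A simulation of steps 3 and 4 with neighbouring inputs (ICC 0.01 to 0.10, groups of 5 or 10, 20,000 replicates per cell) showed the same two directions: 0.050 to 0.040 for an omitted residence effect, and 0.053 to 0.103 for control-session clustering.

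**6. Which test is affected.** These figures concern the group effect over T1-T6. In complete data, a residence or session effect that is constant over time drops out of the time-by-group interaction. Only effects that change over time reach that test.

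**The case against.** The strongest reply is that the article gives one sentence on the model and the analysis plan is not shown, so a residence term may be specified there. If it is, the point is met. But the article states a particular two-way model and a sample size that matches it, so this is a comment on a stated analysis and not on missing detail.

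The second reply is that the sample size reproduces as an interaction test, on which stable intercepts have no bearing. That is correct, and it limits the point. It does not remove it: the model starts at T1, so a benefit already present at six weeks and then stable shows up in the group effect, where residence matters.

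Several stronger readings are tempting and are not supported:

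- *Randomisation took place within residences.* A reader might infer this from the control-group wording, but the text states only individual allocation. If allocation was unrestricted, the model's standard error would be about right on average and the loss would be of precision only.
- *Both arms are clustered by delivery*, which with the same inputs would put alpha at 0.080 to 0.110. Walks are supervised by an assistant, who may be a relative, and group walking is not stated. A subunit's schedule for assistants is not group delivery.
- *Shared nursing-staff raters make the Qualidem and Katz comparisons liberal.* If the same staff rate both arms, the rater effect is common and largely cancels, so leaving it out is conservative. Nothing says that raters differ by arm.
- *The standard errors are known to be too small, or known to be wrong in a given direction.* Every ICC and group size is assumed, and step 5 shows net results on either side of 0.05.

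**Conclusion.** The point holds in limited form. The stated model leaves out a known structure in recruitment and control delivery. For the group effect over T1-T6, omitting residence makes the standard error about 3 to 8% too large if the arms are balanced within residences and the residence ICC is 0.05 to 0.15. Control-session clustering alone would raise alpha to about 0.065 to 0.080 if groups number 6 and the session ICC is 0.05 to 0.10. Under the combinations tried, net alpha lies between about 0.047 and 0.074. The documents fix neither its size nor its direction. This is a worthwhile correction to the analysis model and does not by itself invalidate the trial.

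**What to change.** 1. State how allocation related to residence or subunit, and whether both arms were present in each.
2. Add residence (or subunit; for day-care visitors, the day-care facility) to the repeated-measures model as a random intercept, or as a fixed factor if there are few. If the time-by-group interaction is the test of interest, add residence-by-time as well, since an intercept alone leaves that test unchanged in complete data.
3. Add a sensitivity analysis with a random effect for the control-session group and none for walkers (a partially nested model).

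**Cost.** No new data are needed, since residence is known from recruitment. A random intercept requires a mixed model, whereas a fixed factor fits within a repeated-measures analysis of variance. The main model loses a few degrees of freedom: with an assumed 12 residences, a fixed factor takes 11 of the 140 - 2 = 138 for the group effect. The sensitivity analysis costs more if groups are few. With 70 controls in groups of 6 there are about 12 groups, so the control-arm variance rests on roughly 11 degrees of freedom, which is a reason not to make it the main analysis.

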## Discussion

This paper presents the design of a RCT, which aims to explore the longitudinal effect of regular walking on several health aspects of older people with dementia. The strength of this study is that 1) the intervention is not performed by the research staff, but by the nursing staff which enables it to become a routine in usual care, 2) we have a high number of repeated measurements, i.e. one baseline and 6 post measurements, 3) the various outcome variables enables us to analyse the development of different health aspects within 18 months.

Possible limitations of this study are that 1) only active minded institutions are willing to participate creating a selection bias, 2) there will be a (high) drop-out rate, for example due to death, 3) not all participants will be able to perform/understand all tests.

This method is appropriate to collect data on the effectiveness and feasibility of a walking program. It is also interesting to examine what aspects determine the compliance of the participants. Due to the aging and dementia process, it is not always necessary to increase in test score to find an effect of the intervention, but stabilizing cognitive and behavioural functioning in those who participate in the walking group would also be worthwhile.
